### Possible Limitations of the Study

As it is not a randomized clinical trial, some selection bias could be considered. If the protocol offers positive results, further randomized investigations will be warranted.

It could be difficult to achieve a clear conclusion if the intervention and control group results are very different, although our results from the descriptive analysis of the intervention group will provide relevant information.

We acknowledge that other clinical or psychosocial variables not included in this protocol can influence patients’ needs and satisfaction. We have chosen basic variables that are recorded in the patient’s medical history and are part of the palliative care approach. Depending on the results, we will consider modifying them for future studies in this line of research.

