## Introduction

### Palliative Care in the Community

Palliative care provides professional, scientific, and human responses to the needs of those living with advanced disease or facing the end of life, while also supporting their families [1]. Experts in this field are organized into multidisciplinary teams to provide a comprehensive care model to address suffering, symptom management, and other emotional, social, and spiritual aspects of the final stage of life, death itself, and the grief of relatives [2]. Palliative care is a type of care that best responds to the needs of these people and their families in such circumstances [3] and is internationally recognized as a right of citizens [4]. Palliative care can be provided across multiple settings. Studies indicate that, while aiming to be holistic, palliative care resources cannot possibly cover all patient and family needs [5]. Furthermore, differences in family structure mean that some patients might require more social and practical support than others. In these cases, mobilization of a person’s wider support networks can play a crucial role [6].

The main family caregiver is recognized as the person most involved in the patient’s care. This person, in Latin countries, usually is the contact with health and social care professionals and has to cope with the patient’s daily physical, social, and emotional needs [7]. Outside of the immediate family network, other support networks can assume other necessary tasks [6]. Evidence suggests that up to 7 different profiles have been identified of people who participate in the care of someone facing a terminal illness [8]. Mobilization of this wider network is the base of compassionate communities [9].

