### Variables

The variables we will use for the descriptive study on the REDCUIDA protocol are the following: for patients’ clinical and sociodemographic data: age, sex, and diagnosis; for families’ sociodemographic data: age, sex, and relationship to the patient; for network of care profiles: relationship to the patient, age, and sex; number of needs according to Barthel Index and the Lawton and Brody scale; number of members of the care network; number of needs covered by the network; quality of life according to the quality of life scale EQ-5D-3L; degree of loneliness according to ESTE II Scale; burden of the principal caregiver according to the Zarit Scale; satisfaction regarding the care network according to the Satisfaction Scale; and place of death.

For community promoter activity data, we will determine the number of interventions performed at home and number of interventions carried out in the community (eg, district, neighborhood, city, community of neighbors).

To assess health care system resources, we will determine the number of hospital admissions in the last month; days of hospital stays in the last month; number of emergency visits in the last month; number of visits of the palliative care team to the home; number of visits of the palliative care team to a hospital; and number of telephone calls made by the palliative care team.

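### Two areas are compared with unadjusted tests, and the listed variables omit living arrangement and date of entry to palliative care, leaving avoidable room for confounding

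*Protocol article*

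**What the plan says.** All references are to the protocol article.

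- **Allocation.** Under Recruitment Procedure, intervention patients live in one named area of Seville and accept the community promoter. Controls live in an area that has no promoter.
- **Group comparison.** Statistical Methods compares means by t test or Mann-Whitney test and proportions by chi-square test. A linear regression is mentioned for the pre- and postintervention data of each group, with no covariates named. No adjusted between-group estimate is described.
- **Family structure.** The Introduction (Palliative Care in the Community) says that "differences in family structure mean that some patients might require more social and practical support than others".
- **Patient and family items.** The Variables section opens with patients' "clinical and sociodemographic data: age, sex, and diagnosis", then families' "sociodemographic data: age, sex, and relationship to the patient".
- **Further items in the same list.** Composition of the network appears as "for network of care profiles: relationship to the patient, age, and sex". Dependence enters through the "number of needs according to Barthel Index and the Lawton and Brody scale". Network size and coverage enter through the "number of members of the care network; number of needs covered by the network", and the social and caregiver scales through the "degree of loneliness according to ESTE II Scale; burden of the principal caregiver according to the Zarit Scale".
- **Schedule.** Table 1, in the Intervention section, marks networks of care, Barthel, Lawton-Brody, loneliness and Zarit at V0. EQ-5D-3L is marked only at V6 and satisfaction only at V7.
- **Resource outcomes.** These include the palliative team's home visits, hospital visits and telephone calls.
- **Limitation.** Possible Limitations of the Study accepts that "other clinical or psychosocial variables not included in this protocol can influence" needs and satisfaction. It explains that the chosen variables are basic ones held in the medical history, and leaves changes to later studies.

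**The concern.** When residence decides the group, any difference between the two patient populations that bears on the outcomes enters the comparison as if it were an effect of the promoter. Measured baseline covariates are the main protection, and they work only if they are recorded in both areas and used in the comparison.

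Two factors stand out from the protocol's own reasoning. Family structure is said to affect how much support a patient may need, and unmet need is what the primary objective concerns. Time already spent in the palliative program plausibly drives how often the team visits and calls, and those contacts are outcomes. Neither living arrangement nor program entry date is named in the Variables section.

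If one area has more patients living alone, or more newly referred patients, the difference could be credited to the promoter or held against the promoter. The planned tests have no means of separating the two.

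**Working it through.** **1. What is recorded, set against what is missing**

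| Factor | Named in Variables? | Marked at V0 in Table 1? |
|---|---|---|
| Age, sex, diagnosis | yes | sociodemographic data, by the V0 description |
| Family member's age, sex, relationship | yes | not shown |
| Network size, relationships, needs covered | yes | networks of care: yes |
| Barthel, Lawton-Brody | yes | yes |
| ESTE II, Zarit | yes | yes |
| Lives alone, household size | no | not shown |
| Date of entry to palliative program | no | not shown |

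The network and loneliness measures carry much of the information about support. Relationship and network membership, however, say who helps and not who shares the home. Nothing in the list stands directly for time in the program. Resource use is to be collected before and at the end of the care process, so baseline contacts could absorb part of it.

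**2. Are the V0 measures taken in controls?** Table 1 sits in the Intervention section, and the community promoter completes the V0 referral and requirements sheets. The control area has no promoter. Recruitment Procedure does have palliative teams arrange a baseline assessment, and several scales serve as eligibility conditions, so some control data are likely. The conditions are introduced as alternatives, so not every control need have every scale. Full V0 collection in controls is not stated.

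**3. Is what is recorded used?** The between-group tests in Statistical Methods take no covariates.

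**4. Size, on assumed inputs only.** The documents give no prevalence of living alone and no effect of it. For a binary factor, bias = difference in prevalence between areas × effect of the factor. Assume a difference of 10 to 20 percentage points and an effect of 10 to 30 points on the share of needs uncovered:

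- 0.10 × 10 = 1.0 point
- 0.15 × 20 = 3.0 points
- 0.20 × 30 = 6.0 points

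This is the bias with no adjustment at all; baseline coverage and loneliness would reduce it if used. It cannot be set against the Abstract's 20% effect, because the scale of that percentage is not stated.

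**5. Why partial adjustment matters.** The planned 320 per group reproduces as a headcount: 700 × 0.65 = 455, and 455 × 0.70 = 318.5. Take n = 320 per group, two-sided alpha 0.05 (sidedness is not stated), no true effect, an assumed bias of b standard deviations, and a fraction r of it removed by adjustment. Then SE = √(2/320) = 0.079, d = b(1 − r), and the chance of a significant result is 1 − Φ(1.96 − d/SE) + Φ(−1.96 − d/SE).

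| Assumed bias b | none removed | half removed | three quarters removed |
|---|---|---|---|
| 0.1 SD | 0.24 | 0.10 | 0.06 |
| 0.2 SD | 0.72 | 0.24 | 0.10 |
| 0.3 SD | 0.97 | 0.48 | 0.16 |

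For b = 0.2 and r = 0.5: d = 0.1, d/SE = 1.26, giving 0.24. The table shows direction and sensitivity. It does not predict the bias in this trial.

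**The case against.** The case on the other side has real weight.

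- A reader might infer from the first item of the Variables list that only age, sex and diagnosis are recorded, and so that no adjusted analysis could deal with family structure. The documents do not support this. The same list has family relationship, network size and composition, needs covered, two dependence scales, loneliness and caregiver burden, most of them marked at V0. An adjusted comparison could remove some of the confounding, perhaps much of it.
- A reader might also call family structure the main confounder. No section ranks confounders, and the Introduction says only that some patients might need more support.
- The article is condensed. V0 covers sociodemographic data on a referral sheet (Multimedia Appendix 1) that is not shown and may already hold these items. This stands, and the fix allows for it.
- Program entry date could probably be taken from the medical record later, so that gap may be repairable. This also stands. Household composition is less surely recoverable after a patient's death.
- The limitation is disclosed, and it is not an error. Agreed; but disclosure does not reduce the bias, and the remedy is cheap if made before enrolment.
- Covariates may be left to an analysis plan. In general that is fair, but the article does specify how the groups will be compared, and it specifies unadjusted tests.

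**Conclusion.** The point holds in a limited form. Groups are formed by area and compared with unadjusted tests. The listed variables do not name living arrangement or time in the palliative program, and baseline collection in controls is not explicit. Residual confounding of unmet needs, loneliness, burden and team contacts by these factors is possible. It matters most for EQ-5D-3L and satisfaction, which have no V0 value in Table 1 to adjust for.

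The size cannot be derived from the documents. The 1 to 6 points and the rejection rates above rest wholly on assumed inputs. The documents do not show that the two areas differ in these factors, nor that the confounding is beyond adjustment. Even with the added items, area and treatment remain fully aliased, so other unmeasured area differences cannot be excluded.

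**What to change.** 1. Record three items at V0 in both areas: lives alone (yes/no), household size, and date of entry to the palliative program, the last from the medical record. If Multimedia Appendix 1 already holds them, confirm this and name them in the Variables section.
2. State that the V0 measures in Table 1 are taken in controls too, and by whom, since the control area has no promoter. Values taken after the intervention has begun cannot serve, because the intervention may change them.
3. Estimate the between-area effect from a regression that adjusts for the three items, age, sex, diagnosis, and the baseline Barthel, network, loneliness and Zarit values. The unadjusted tests can stay as descriptive results.
4. Keep the statement in Possible Limitations of the Study: it remains true after these additions.

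Cost: a few short items per patient, one of them from the record; baseline assessment time in the control area where it is not already planned; and slightly more analysis work.

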### Conclusions

This is, to our knowledge, one of the first trials to measure the effectiveness of a nonprofessional network intervention on patient and family satisfaction, family burden, and use of heath resources.

The results of this study may provide some directions for future palliative care interventions at the community level with frail populations. These interventions may also provide a basis for training health professionals and social resources to improve patient–professional communication about end-of-life care for patients at home and stimulate the development of systematic palliative care community networks for this population.

## Appendix

Multimedia Appendix 1 REDCUIDA protocol: inclusion and referral of the beneficiary.

Multimedia Appendix 2 REDCUIDA protocol: beneficiary's scale of needs (adapted from Mahoney and Barthel [29]).

Multimedia Appendix 3 Circle of the community network.

Multimedia Appendix 4 ESTE II Loneliness Scale.

Multimedia Appendix 5 EQ-5D-3L quality-of-life scale.

Multimedia Appendix 6 Zarit Scale for caregiver burden.

Multimedia Appendix 7 Family and social support network scale of satisfaction.

Multimedia Appendix 8 Questionnaire on use of the health care system.

## Abbreviations

EQ-5D-3L: 3-level EuroQol 5 dimensions questionnaire
ESTE II: Scale of Social Loneliness II
REDCUIDA: *Redes de Cuidados* (Network of Care)
